### Study design

This double-blind, multicenter, parallel-group, superiority, 1:1 randomization ratio prospective clinical study was approved by the Institutional Review Board of the First Affiliated Hospital of Henan University of Chinese Medicine (reference number 2017HL-069-01, validated on 22 November 2017) and registered at ClinicalTrials.gov (NCT03428412). The protocol follows the recommendations of the Standard Protocol Items: Recommendations for Interventional Trials (SPIRIT) initiative (Additional file 1) [7].

The flowchart of the study process is detailed in Fig. 1. The timing of treatment visits and data collection is detailed in Table 1.

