### Randomization and blinding

A central dynamic stochastic distribution method is adopted. The randomization sequence will be generated by the ‘proc plan’ procedure of SAS software (version 23.0) according to stratified block randomization with a block size of 6, and the random number and group assignment will be obtained from a central randomization system provided by Jiangsu Famous Medical Technology Co., Ltd. in Nanjing, China. Eligible AECOPD patients will be randomly divided into an experimental group and a control group in a 1:1 allocation ratio. The data management and statistical analysis units formulate a random distribution scheme according to the test scheme. They then implement and manage the random distribution scheme through a central random distribution interactive voice operating system. The researcher obtains the subject assignment code via the Internet or phone.

All participants, trial participants, care providers, and outcome assessors except for the data analysts are blind to treatment allocation. The CM placebo packaging in the control group is consistent with the CM granules, and the odor and color are also similar to those of the experimental group CM granules, but there is no clinical effect. If serious adverse events that threaten the safety of participants occur, we will immediately stop the intervention, cancel the blinding, and contact the Institutional Review Board.

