#### Chinese medicine

On the basis of health education and conventional drug treatment, the intervention group will be treated with CM, and the control group will be given a CM placebo. According to traditional CM syndromes, Sanhanhuayin granules are given for the syndrome of external cold and internal fluid, Qingrehuatan granules for the syndrome of phlegm-heat congesting the lung, and Zaoshihuatan granules for the syndrome of phlegm-damp amassing in the lung. Both the CM and the CM placebo granules come in bags, 10 g/bag, which are produced by Jiangyin Tian Jiang Pharmaceutical Co., Ltd. Test results of drug quality were consistent with the required quality standards. Each type of granule will be given orally, twice a day, for 14 days. The dose of the drug is not allowed to be modified.

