### Statistical analysis

All data will be analyzed according to the intention-to-treat (ITT) and per-protocol (PP) analyses to reduce deviation. The modified intention-to-treat (mITT) analysis set is a subset of the ITT population and allows the exclusion of some randomized subjects in a justified way. The PP analysis set will include patients who fully complete the trial. The mITT analysis set is used for efficacy and the PP analysis set for safety. Continuous variables will be presented as mean and standard deviation or median and interquartile range according to the Kolmogorov-Smirnov test, and categorical variables as number of patients and proportion.

The Student’s *t* test will be used to compare differences in measurement data. The rank sum test will be used to deal with ranked data, the chi-squared test will be used to analyze categorical data, and the repeated measures analysis of variance (ANOVA) test will be used to analyze multiple measurements at different time-point data. If the effect of the different centers is significant, the Cochran-Mantel-Haenszel (CMH) chi-square test or analysis of covariance (ANCOVA) test is used to correct it. A statistician not involved in data collection will conduct all statistical analyses using SPSS version 23.0 software (SPSS Inc., Chicago, IL, USA).

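### Randomisation is stratified, yet the plan analyses without strata by default and lets an unspecified test of the centre effect decide whether to adjust

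*Protocol article*

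**What the plan says.** Under Study design the trial is described as "This double-blind, multicenter, parallel-group, superiority, 1:1 randomization ratio prospective clinical study". Under Randomization and blinding, the sequence is generated "according to stratified block randomization with a block size of 6", and patients are "randomly divided into an experimental group and a control group in a 1:1 allocation ratio". The stratification factors are not named. The same section also says "A central dynamic stochastic distribution method is adopted", which sits awkwardly beside a pre-generated block list.

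Under Statistical analysis the default methods take no account of strata. For continuous data, Student's t "test will be used to compare differences in measurement data". For the rest, "The rank sum test will be used to deal with ranked data, the chi-squared test will be used to analyze categorical data", with repeated measures ANOVA for outcomes measured at several times. Adjustment enters by one rule only: "If the effect of the different centers is significant, the Cochran-Mantel-Haenszel (CMH) chi-square test or analysis of covariance (ANCOVA) test is used" to correct for centre. The section does not say how the centre effect is tested or at what level it counts as significant.

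Under Chinese medicine, the syndrome fixes the product; for example, "Sanhanhuayin granules are given for the syndrome of external cold and internal fluid", with two other granules for the other two syndromes.

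**The concern.** There are two separate faults.

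First, a significance test on the trial's own data selects the analysis. The CAT comparison has two candidate p-values, one unadjusted and one adjusted, and which becomes the result is unknown until the outcomes are in. Because neither the test nor its level is stated, two analysts following the text could end up with different primary analyses.

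Second, the default analysis does not match the design. Stratified blocks balance the arms within strata, which removes between-stratum variation from the treatment difference. An unadjusted test leaves that variation in its error term, so the standard error is too large and the confidence interval too wide whenever the strata predict outcome. For centre, the conditional rule may repair this. For any other stratification factor, the stated rule offers no repair.

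At stake are precision, a modest amount of power, and whether the primary result can be called prespecified.

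**Working it through.** **Inputs.** From Sample size: two-sided α 0.05 (z = 1.96), power 90% (z = 1.28), difference 2 CAT points, SD 5.50 for CM, 170 per group before dropout. The placebo SD is 5.78 where the formula is filled in and 5.87 where the earlier study is reported. Assumed, because the article does not give them: the share of CAT variance explained by the strata, the number of strata, and the level of the centre pretest.

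**Reproducing the plan's figure.** n = (1.96 + 1.28)² × (σ₁² + σ₂²) / 2².
- σ₂ = 5.87: 10.4976 × 64.7069 / 4 = 169.8, so 170.
- σ₂ = 5.78: 10.4976 × 63.6584 / 4 = 167.1, so 168.

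170 / 0.9 gives 189 per group, 378 in total. The formula is the unadjusted two-sample one. I use 5.87 below because it returns 170.

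**Cost of leaving out a factor that was stratified on.** The unadjusted SE is √(64.7069 / 170) = 0.617, and 2 / 0.617 = 3.242. Let R² be the share of variance explained by the omitted strata, with the total SD held fixed. The true SE of the difference is then 0.617 × √(1 − R²), so with k = 1/√(1 − R²):
- SE ratio = k
- true two-sided error of the nominal 5% test = 2 × [1 − Φ(1.96k)]
- unadjusted power = Φ((3.242 − 1.96)k)
- adjusted power = Φ(3.242k − 1.96)

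| R² (assumed) | SE ratio | True error | Unadjusted power | Adjusted power |
|---|---|---|---|---|
| 0 | 1.000 | 5.0% | 90.0% | 90.0% |
| 10% | 1.054 | 3.9% | 91.2% | 92.7% |
| 20% | 1.118 | 2.8% | 92.4% | 95.2% |

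Before rounding, the power gaps are 1.6 and 2.8 points; with σ₂ = 5.78 they are 1.5 and 2.7.

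**What the stated rule does for centre.** The table compares never adjusting with always adjusting; the plan does neither. The rule itself was simulated: 4,000 trials per setting, 340 evaluable patients, one continuous outcome with SD 5.64, blocks of 6 within 6, 10 or 20 equal strata, and adjustment only if the stratum F test gave p < 0.05. ICC is the share of outcome variance lying between strata.

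| ICC (assumed) | Rule picks adjusted model | Unadjusted test: mean SE / true SD | Unadjusted test: type I error |
|---|---|---|---|
| 0 | about 5% | about 1.00 | about 0.05 |
| 0.02 | 25–40% | | |
| 0.05 | 63–73% | | |
| 0.1 | 91–94% | 1.04–1.07 | 0.036–0.042 |
| 0.2 | 97% or more | 1.09–1.12 | 0.032–0.034 |
| 0.3 | 99% or more | 1.14–1.18 | 0.022–0.027 |

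Across all settings the rule's overall type I error was 0.039–0.057 (Monte Carlo standard error about 0.0034), against 0.040–0.057 for always adjusting. Its power was within 0.003 of always adjusting. The choice of model is least predictable at ICCs of 0.02 to 0.05, where little power depends on it.

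**The case against.** The strongest reply is that the rule adjusts for centre when it matters. At an ICC of 0.1 it picks the adjusted model in more than nine trials in ten, and the power lost is negligible. This stands: for centre, the figures in the first table must not be read as the cost of the plan's rule. They apply only to a stratified factor that the rule leaves out.

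A second reply is that even unadjusted power exceeds the planned 90% in those settings. This also stands. A reader might infer that the trial is underpowered or that its false-positive rate is inflated; neither follows. The error in the SE is conservative, it vanishes if the strata are not prognostic, and the selector is the centre effect, not the treatment result.

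A third reply concerns syndrome. Because it determines the product, a reader might take it to be a stratum and add its variance to the SE error. The article names no stratum. If syndrome was not stratified on, the unadjusted SE is not biased by it. Nor is the absence of syndrome-specific estimates or an interaction test a fault here, since a condensed article commonly leaves these to the analysis plan, which Data management says will be written.

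That reply does not cover the conditional rule. The article states it outright, and an analysis plan that followed the article would inherit it.

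**Conclusion.** The point holds as one of prespecification and of matching analysis to design. The text lets the data choose between an unadjusted and a centre-adjusted analysis, with no test or level given, and its rule never adjusts for a stratification factor other than centre.

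The size depends on strata that are not named. If some factor besides centre was stratified on and explains 10% to 20% of CAT variance, the standard error is about 5% to 12% too large and about 1.5 to 2.8 percentage points of power are given up. If centre is the only stratum, which is itself an inference from the multicentre design, the numerical loss is small under every setting tried and the data-driven choice is the main fault. The simulation rests on equal strata, a single continuous outcome and an assumed pretest level of 0.05. The change is worth making because it costs almost nothing; the fault does not threaten the trial's validity.

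**What to change.** Under Statistical analysis, delete the condition that the centre effect be significant. Prespecify one primary model for CAT that always includes the stratification factors used by the central randomisation system and baseline CAT, whatever any centre test shows. Use CMH stratified by the same factors for binary outcomes. State in advance how small centres are pooled.

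Under Randomization and blinding, name the stratification factors and reconcile the dynamic method with the pre-generated block list, so that the model can be matched to the allocation actually used.

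Syndrome may be added as a baseline covariate because it determines the product given, but it should not be described as a stratum unless the randomisation system used it. Syndrome-specific estimates are optional and supportive. Baseline CAT is not needed to cure the conditional rule; it is a free gain in precision, since Table 1 already schedules CAT at baseline.

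The cost is wording and a pooling rule. Sample size and data collection are unchanged.

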### Clinical trial registration

This trial was registered at ClinicalTrials.gov on 4 February 2018 (NCT03428412).

## Discussion

AECOPD are important events in the management of COPD because they negatively impact health status and rates of hospitalization and readmission, and potentially result in death and functional disability [22, 23]. The goals of treatment for AECOPD are to minimize the negative impact of the current exacerbation and prevent the development of subsequent events. The chemical medications most commonly used for AECOPD are bronchodilators, corticosteroids, and antibiotics. CM is used extensively in the treatment of AECOPD in Asia, particularly in China. The effects of CM, especially herbal medicines, in improving respiratory symptoms and decreasing the incidence of COPD exacerbations are well known.

Clinical studies have postulated that herbal medicine is effective as a supplemental remedy for treating AECOPD [8, 24]. However, due to the single type of syndrome, limited sample sizes, or methodological problems apparent in some studies, the evidence for the effectiveness of CM was not robust. This RCT will investigate the effectiveness of CM in the treatment of AECOPD. We are attempting to conduct a clinical RCT with adequate design and few deficits. We performed a multicenter, randomized, double-blind, placebo-controlled clinical trial to assess the beneficial or harmful effects of CM for treating AECOPD.

An exacerbation of COPD is defined as an acute worsening of respiratory symptoms that result in additional therapy. The key symptom of an exacerbation is increased dyspnea. Other symptoms include increased sputum purulence and volume, together with increased coughing and wheezing [25]. We thought that if CM is effective in reducing increased dyspnea, cough, and sputum caused by exacerbation, it may primarily affect the respiratory symptoms, so we consider this as the primary outcome of our trial. We also examine the incidence of treatment failure and intubation, length of hospital stays, readmission due to exacerbation, number of deaths, and quality of life to obtain more evidence for AECOPD with CM. Therefore, we hope this trial will provide useful evidence for developing a therapeutic schedule with CM for patients with AECOPD.

### Trial status

The current protocol is version 8.0, 16 October 2018. The study began recruiting in August 2018. At the time of manuscript submission, we have recruited 36 patients. The recruitment of participants has now been completed. Follow-up assessments of patients are expected to be completed in January 2020. A populated SPIRIT checklist is available as Additional file 1.

## Abbreviations

AECOPD: Acute exacerbations of COPD
CAT: COPD Assessment Test
CM: Chinese medicine
COPD: Chronic obstructive pulmonary disease
COPD-PRO: COPD patient-reported outcome scale
GOLD: Global Initiative for Chronic Obstructive Lung Disease
mMRC: Modified (British) Medical Research Council
RCT: Randomized controlled trial
SF-36: 36-item Short Form Health Survey
